**2.5 Economic appraisal**

Insufficient and inadequate economic evaluation of educational interventions creates uncertainty in the decision to adopt trials of implementation research with positive results (Brown 2002; O’Brien 2002; Beney 2004). Based on available evidence, there is insufficient information indicating cost effectiveness. However, Soumerai evaluated the cost effectiveness of academic detailing within a randomised controlled trial and found it to be highly cost effective. Two meetings lasting approximately 18 minutes each, between a trained detailer and GP, were focussed on three drug groups commonly used inappropriately. They found that target drug use was decreased beyond the point where the model became cost effective. They also observed that the reduction was not affected by pre-intervention prescribing levels (Soumerai 1986).

Watson delivered educational outreach visits to GPs in England and found the costs of delivery were greater than the costs saved as a result of the (statistically insignificant) prescribing changes observed (Watson 2002). However, in this study based in 20 general practices in England, the team delivering the intervention did not explicitly make any recommendations of a cost saving nature which is unusual for pharmacist-led prescribing support in the UK. Without cost saving as one of the key outreach messages, and without an endpoint associated with significant costs (from an NHS perspective) e.g. hospitalisations, it is less of a surprise that cost effectiveness was unproven. May et al also found this to be the case in 1999.

Possibly the most detailed study of the cost effectiveness of outreach visiting was described by Mason (2001). Their perspective was that of the policymaker faced with the decision to implement guidelines on ACE inhibitors for heart failure and tricyclic antidepressants rather than newer, more expensive SSRI antidepressants. While their analysis, like the original publication (Nazareth 2002), is at times difficult to follow, it appears that their model of outreach became cost effective if the focus was on improving quality (increasing ACE inhibitor use in heart failure) but not for cost saving (tricyclic instead of SSRI antidepressants). Key reasons behind this were discussed and included the large health benefit achievable through the use of ACE inhibitors in heart failure while the relatively small cost savings accrued by switching antidepressants did not offset the cost of the outreach visits. Acknowledging that the process of implementation of best practice in prescribing incurs a cost, Mason summarised the importance of evaluating the policy cost effectiveness of prescribing change models, and argued for the measurement of costs to form part of implementation research design.

**3. Study methods**

**3.1 Setting - NHS Greater Glasgow & Clyde**

At the start of the SOS trial (2003), NHS GG&C existed as two geographically and organisationally separate Board areas: Greater Glasgow Health Board and Argyll and Clyde Health Board. In 2006, Argyll and Clyde Health Board split and the Argyll area merged with Highland Health Board. Greater Glasgow Health Board absorbed the Clyde component, and was renamed GG&C Health Board. The SOS trial involved practices and policies within Greater Glasgow only.

NHS GG&C Health Board provides health care to almost 25% of the Scottish population. The GG&C population lives within a diverse geographical area, encompassing both urban and rural settings and suffers high levels of deprivation and unemployment with the worst health status and most extreme health inequalities in Scotland. Although overall life expectancy is increasing, the population faces a growing burden of morbidity and disability driven by LTCs. In addition, the Board area continues to attract an increasing migrant population, with their own health challenges. LTCs account for over 80% of total general practice consultations and 60% of hospital bed days (Department of Health 2004). Cardiovascular Disease (CVD), cancers and chronic respiratory disease account for the majority of premature deaths. In the Board’s Director of Public Health Report (2009), the following key health problems were identified:

- CVD;
- Health inequalities;
- Substance Misuse (drugs, alcohol and smoking);
- Obesity.

A substantial proportion of CVD risk is attributable to high cholesterol and some of this is preventable through prescribing of statins in accordance with robust evidence from clinical trials. CVD encompasses several distinct conditions e.g. Coronary Heart Disease (CHD). Other conditions sharing the same vascular pathophysiology include stroke, Transient Ischaemic Attack (TIA), Peripheral Vascular Disease (PVD) and Diabetes. Underlying coronary vascular disease is the most common reason for Coronary Artery Bypass Graft (CABG) and Angiography, which classifies patients who have undergone these procedures as being at equivalent risk as patients with CHD. CHD is the largest subgroup of CVD and as such, is a strong predictor of CVD trends. A summary of the combined prevalence and impact of vascular disease within GG&C was not available. However, age standardised CHD death rates were available and are described in Fig 1. While the prevalence of CHD is decreasing, in GG&C Health Board it remains the leading cause of death, with rates consistently above the National average (Figure 1).

**Figure.1 Coronary Heart Disease Death rates in NHS GG&C**

[figure not shown]

Several factors could have accounted for the steep decline in death rates in GG&C and the rest of Scotland over this period. These include improved primary and secondary prevention of CHD e.g. improved prevention and management of hypertension or myocardial infarction (Capewell 1999). Decreases in blood pressure over this period were confirmed by data from the Scottish Centre MONICA studies, with additional data showing reductions in smoking prevalence and cholesterol levels between 1976 and 1996 (Evans 2001).

The Heart Protection Study and derived GG&C guidance offered an opportunity to further tackle the burden of CHD and other vascular mortality for patients with vascular disease, because of the finding that simvastatin 40mg daily for 5 years reduced the rates of heart attack, stroke and revascularisation by approximately 25%. While cholesterol decreased in HPS, the use of simvastatin 40mg was sufficient to achieve benefit without cholesterol reduction.

The challenge for GG&C and other health care providers is to maximise the uptake of robust evidence based treatments such as this.

**3.2 Aim of study**

The aim of the study is to evaluate the effectiveness of pharmacist-led SOS intervention delivered at the level of general practices, to practice staff. The SOS study will therefore test the hypothesis that primary care, general practice based pharmacists delivering the SOS intervention at practice level, can increase the proportion of patients with their cholesterol controlled, compared with care as usual.

**3.3 Endpoints**

The primary endpoint is the proportion of patients with cholesterol controlled, evaluated at the level of the individual patient, in the SOS intervention arm practices compared with Usual Care (UC). Secondary endpoints are:

- Prescribing of simvastatin;
- Prescribing of Simvastatin 40mg with cholesterol control;
- Prescribing of simvastatin 40mg;
- Cholesterol tested since randomisation for patients prescribed simvastatin 40mg;
- Cholesterol levels of patients prescribed simvastatin 40mg;
- Cholesterol levels tested since randomisation;
- Cholesterol levels;
- Prescribing of any statin.

Outcomes will be assessed between 1.4 and 2.2 years (mean 1.7 years) after randomisation.

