**3.5 Statistical analysis**

Pilot work found 50% of patients to have cholesterol controlled with an intraclass correlation (ICC) of 0.4. Assuming that data for 40 patients per practice would be collected, we estimated that approximately 20 practices (10 per group) would be required to detect an increase in cholesterol control to 90% in intervention practices. We anticipated a high practice dropout rate due to the length and intensity of the intervention. We, therefore, invited 49 practices to participate.

Analysis will be by intention to treat. Descriptive statistics for continuous variables will be presented as mean and standard deviation and for categorical variables, as frequencies and percentages. Baseline analysis will compare participating with non-participating practices, SOS with UC practices, and single handed with group practices. Patient level data will not be collected for non-participating practices. Summaries will use continuous and categorical variables, as appropriate. Practice-level data (e.g. number of GPs, list size) will be compared using the Wilcoxon-Mann-Whitney test, or, for comparisons between SOS and UC practices, using the Wilcoxon Signed Rank test within pairs of practices.

Due to the non-normal distribution of cholesterol levels, a log-transformation will be applied. Patient level data will be analysed at the individual level for greater power.

Linear and logistic regression models will be used to test for differences in the primary and secondary outcomes between the two intervention groups. These models will be adjusted for practice pair to account for the matching at randomisation. Results will be presented as intervention effect or odds ratio, 95% confidence interval and p-value. Secondary analyses will be carried out to investigate the sensitivity of the results to adjustments for age and sex. A sensitivity analysis, adjusting for any statin prescribing at follow up, will be carried out for the primary outcome to assess whether the treatment effect can be explained by increased statin prescribing.

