**3.8 Participating practices and patients**

Practices will be asked to identify patients who had confirmed vascular disease. These patients are at ≥ 30% risk of suffering a cardiovascular, cerebrovascular or peripheral vascular event in the next 10 years. In accordance with GG&C Cholesterol Guidelines (Appendix III), this level of risk will be confirmed by the following confirmed diagnoses:

- Myocardial infarction;
- CABG / angioplasty;
- Angina/IHD;
- Angiographic coronary artery disease;
- Stroke/transient ischaemic attack;
- Peripheral ischaemic arterial disease/intermittent claudication;
- Diabetic patients aged over 45years.

A validated computer search of each general practice’s computerised patient record will generate a list of eligible patients. Each patient’s computerized and paper record will then be screened to collect relevant data.

Due to time and resource limitations, a systematic sample of every third eligible patient’s data will be collected in 5 practices with the largest list sizes (12330, 7354, 7215, 7099 and 5616 patients). Therefore, cross sections of data will be collected at baseline. In addition, in all practices, some demographic data (in particular, the “Patient identification number”) may not be available. Both factors preclude longitudinal follow up of all patients. In all practices, data will be collected from each eligible patient’s record, anonymised in the practice and entered onto an ACCESS database.

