**Blinding**

In common with trials of other educational interventions, double blinding was not possible. The study will be assessor blind, because baseline data will be collected before allocation. At follow up, two independent researchers will collect prescribing and cholesterol outcome data. Both will be blinded to whether practices had received the SOS intervention or UC, therefore bias in the process of data collection will be minimised.

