**Appendix IV**

**Clinical Facilitation**§**: a summary for practices**

This is a multifaceted intervention, rooted in the belief that more intensive efforts to alter prescribing practice are generally more successful. Clinical Facilitation involves prescribing support pharmacists meeting individually with GPs or nurses to identify any obstacles standing in the way of offering patients statins to lower cholesterol and then providing specific, practical solutions (facilitation) to overcome these obstacles. Some techniques used to change prescribing include: implementation of the evidence may include a practice based clinical audit; open, honest communication; agreement on help needed by the practice to improve patient attendance. Increasing prescribing of simvastatin 40mg for patients with vascular disease will feature in each meeting.

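### Two secondary endpoints and the statin-adjusted model condition on prescribing that SOS is designed to change, so they are not randomised comparisons

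*Protocol*

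**What the plan says.** Section 3.3 lists eight secondary endpoints. Two are confined to a prescribing subset: "Cholesterol tested since randomisation for patients prescribed simvastatin 40mg" and "Cholesterol levels of patients prescribed simvastatin 40mg". Prescribing of simvastatin 40mg and prescribing of any statin are also endpoints in the same list.

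The protocol does not date the prescribing that defines the subset. Three statements bear on it:
- Section 3.3: "Outcomes will be assessed between 1.4 and 2.2 years (mean 1.7 years) after randomisation".
- Section 3.9, Blinding: "At follow up, two independent researchers will collect prescribing and cholesterol outcome data".
- Section 3.8, on sampling in the largest practices and missing patient identifiers: "Both factors preclude longitudinal follow up of all patients".

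The intervention acts on this variable. Section 4.1.1 has pharmacists find eligible patients who are not on simvastatin 40mg and help the practice decide whether and how to introduce it. Appendix IV states: "Increasing prescribing of simvastatin 40mg for patients with vascular disease will feature in each meeting".

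In section 3.5 the principle is "Analysis will be by intention to treat". Linear and logistic models then test primary and secondary outcomes between arms, giving an effect or odds ratio, confidence interval and p-value. The section adds: "A sensitivity analysis, adjusting for any statin prescribing at follow up, will be carried out for the primary outcome". Its stated aim is to see whether more statin prescribing accounts for the effect.

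**The concern.** If SOS works, the patients on simvastatin 40mg at follow-up in SOS practices include people who would not have been on it under usual care. The two subsets are then different kinds of patient, and a difference between them mixes any effect of SOS with a difference in who was selected. Selection is also tied to cholesterol: Appendix III moves patients who miss their goals to another statin, and Table 2 ties several actions to the cholesterol result or its absence. Nothing in section 3.5 separates these two endpoints from the all-patient ones, so their p-values would read as intervention effects.

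The adjusted model raises a related problem. Any-statin status at follow-up lies between allocation and outcome. The adjusted odds ratio could be read as the part of the effect not due to statins, although the model cannot isolate that part.

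**Working it through.** **Plan's own figure.** The protocol gives no number for these endpoints. Its one design calculation concerns the primary endpoint and is not in dispute. The design effect is 1 + 0.4 × 39 = 16.6. Assuming two-sided 5% and 85% power (neither is stated), 50% v 90% needs 22 per arm, and 22 × 16.6 / 40 = 9.1, so 10 practices per group, as stated.

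All inputs below are assumptions. They show what can happen, not what will.

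**1. Cholesterol level among those prescribed.** Let p0 and p1 be simvastatin 40mg prescribing in usual care and SOS. Let d be the on-treatment difference between patients added by SOS and those prescribed anyway, and let SOS have no effect on the latter. Then:
- added share of the SOS subset = (p1 − p0)/p1
- difference among the prescribed = share × d
- all-patient effect = −(p1 − p0) × 0.8, if each added patient falls by 0.8 mmol/l

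| p0 / p1 | Added share | d = +0.3 | d = +0.5 | All-patient effect |
|---|---|---|---|---|
| 30% / 50% | 0.40 | +0.12 | +0.20 | −0.16 |
| 30% / 60% | 0.50 | +0.15 | +0.25 | −0.24 |
| 40% / 50% | 0.20 | +0.06 | +0.10 | −0.08 |

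Negative d reverses the restricted differences. At 30%/50% and d = −0.5 the result is −0.20, which overstates the benefit.

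**2. Testing among those prescribed.** Take 30% v 50% prescribed, with 90% of those already prescribed tested, and suppose SOS changes nobody's testing. If added patients are tested at 60%, SOS shows (0.30 × 0.90 + 0.20 × 0.60)/0.50 = 78% against 90%. At 98% it shows 93.2% against 90%. Over all eligible patients, prescribed and tested is 0.30 × 0.90 = 27% in usual care, against 39% (27% + 12%) or 46.6% (27% + 19.6%) in SOS.

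**3. Adjusting for any statin: shared causes.** Let U be an unmeasured factor held by half the patients, with logit P(statin) = 0.6 + b(U − 0.5) + 1.0·SOS and logit P(control) = −0.7 + 1.4·statin + c(U − 0.5) + g·SOS. Fitting control on arm and statin to the exact expected counts gives:

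| b, c, g | Statin use | Unadjusted OR | Adjusted OR |
|---|---|---|---|
| 0, 0, 0 | 64.6% v 83.2% | 1.29 | 1.00 |
| 2, 1.5, 0 | 61.7% v 78.8% | 1.23 | 0.89 |
| −2, 1.5, 0 | 61.7% v 78.8% | 1.23 | 1.11 |
| 2, 1.5, 0.1 | 61.7% v 78.8% | 1.33 | 0.97 |

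With no direct effect (g = 0), the adjusted odds ratio can fall on either side of 1. With a small direct benefit (g = 0.1, OR 1.11), it falls below 1. Section 4.1.2 itself names possible shared causes of statin use and control, such as missed appointments and patients ceasing to order prescriptions. The model adjusts for none of them.

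**4. Non-collapsibility.** Take logit P(control) = −1.5 + 2.5·statin + ln 2·SOS, so the conditional OR is 2.0.
- Statin use 70% in both arms (no mediation): control is 56.6% v 68.4%, a crude OR of about 1.66. Adjustment moves it to 2.0 although nothing is mediated.
- Statin use 70% v 80%: control is 56.6% v 73.7%, a crude OR of 2.15. The log OR falls by (0.765 − 0.693)/0.765 = 9%. On the risk scale, (73.7 − 68.4)/(73.7 − 56.6) = 31% of the difference runs through added statin use.

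**5. What any-statin yes/no records.** Of the five patient categories in section 4.1.4, only one is untreated. A change of drug or dose in an already treated patient leaves the variable unchanged, so that route would count as effect not due to statins.

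**The case against.** **Timing is inferred.** Only the adjusted model says follow-up outright. The protocol rules out linkage for all patients, not for every patient, and its subgroup list does use baseline statin status. If baseline prescribing were meant, SOS could not have altered it and the point on these two endpoints would fall. However, cross-sectional data and newly diagnosed patients make that reading unworkable for the whole sample.

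**Reach is limited.** Two of eight secondary endpoints and one supporting analysis are affected. Unrestricted testing, level and prescribing endpoints sit in the same list. This stands, and it makes the point modest.

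**The mediation aim is declared.** Asking the question is legitimate, and any-statin status is a natural variable for a question about more statin prescribing. Appendix III also recommends a statin whatever the cholesterol level, so yes/no status should depend on the result less than drug or dose does. This stands, and it means that substituting type and dose would not remove confounding.

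**Stronger readings a reader might infer are not supported.** The protocol does not show that the restricted comparisons would make SOS look harmful, because the bias can go either way or be zero. It gives no usual-care prescribing rate, so it cannot be said that few usual-care patients take simvastatin 40mg. It does not rank switching above starting a statin as the main route. The primary comparison is not compromised.

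**Conclusion.** The point holds in a limited form. The two restricted endpoints are not randomised comparisons, provided the subset is defined at follow-up, yet the plan tests them as if they were. The statin-adjusted model is a mediation analysis labelled as a sensitivity analysis, and adjustment alone cannot show whether statin prescribing explains the effect. The examples establish only that the sign can reverse. The magnitudes of 0.06 to 0.25 mmol/l, and adjusted odds ratios from 0.89 to 1.11 with no direct effect, rest wholly on assumed inputs. The primary endpoint and the endpoints not restricted by prescribing are outside this finding.

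**What to change.** - State when the prescribing that defines the subset is measured.
- Define the testing endpoint on all eligible patients: prescribed simvastatin 40mg and cholesterol tested since randomisation, yes or no.
- Base inference on cholesterol level on the unrestricted level endpoint already in section 3.3. State that it still depends on who was tested, which SOS also changes through the blood-test letters in Table 2. It reduces the problem without curing it.
- Report the figures within the simvastatin 40mg subset descriptively, with no between-arm test or p-value.
- Relabel the statin-adjusted model exploratory and state its assumption of no unmeasured common causes of statin use and control. Show it on the risk-difference scale beside the SOS effect on the prescribing categories of section 4.1.4. Do not conclude from it alone that the effect is, or is not, explained by statin prescribing.

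The cost is a change of wording. No new data are needed if follow-up prescribing is recorded by drug and dose, as the simvastatin 40mg endpoints already require for that drug. The trial gives up two tests within the prescribed subset and gets a more modest answer on the role of statins.

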**3.4 Sample size and power**

Cluster randomised trials require larger numbers of individuals because there tends to be correlation of outcomes within clusters which otherwise reduces the statistical power, compared to individually randomised trials. The method of calculation of sample size is a key difference between a practice randomised trial and an individually randomised trial: the sample size needs to increase to accommodate clustering, using a cluster inflation factor (also called the design effect, D). The design effect is related to the cluster size (m, the number of patients in each cluster) and the intra cluster correlation coefficient (ρ, which measures the size of the clustering effect i.e. the correlation of patient outcomes within a cluster) by the equation:

D = 1 + ρ (m – 1)

The design effect enables calculation of the amount by which the sample needs to be multiplied, to maintain sufficient power.

**3.5 Statistical analysis**

Pilot work found 50% of patients to have cholesterol controlled with an intraclass correlation (ICC) of 0.4. Assuming that data for 40 patients per practice would be collected, we estimated that approximately 20 practices (10 per group) would be required to detect an increase in cholesterol control to 90% in intervention practices. We anticipated a high practice dropout rate due to the length and intensity of the intervention. We, therefore, invited 49 practices to participate.

Analysis will be by intention to treat. Descriptive statistics for continuous variables will be presented as mean and standard deviation and for categorical variables, as frequencies and percentages. Baseline analysis will compare participating with non-participating practices, SOS with UC practices, and single handed with group practices. Patient level data will not be collected for non-participating practices. Summaries will use continuous and categorical variables, as appropriate. Practice-level data (e.g. number of GPs, list size) will be compared using the Wilcoxon-Mann-Whitney test, or, for comparisons between SOS and UC practices, using the Wilcoxon Signed Rank test within pairs of practices.

Due to the non-normal distribution of cholesterol levels, a log-transformation will be applied. Patient level data will be analysed at the individual level for greater power.

Linear and logistic regression models will be used to test for differences in the primary and secondary outcomes between the two intervention groups. These models will be adjusted for practice pair to account for the matching at randomisation. Results will be presented as intervention effect or odds ratio, 95% confidence interval and p-value. Secondary analyses will be carried out to investigate the sensitivity of the results to adjustments for age and sex. A sensitivity analysis, adjusting for any statin prescribing at follow up, will be carried out for the primary outcome to assess whether the treatment effect can be explained by increased statin prescribing.

Subgroup analyses of differences in endpoints between SOS and usual care groups will be defined by the following baseline variables: age, gender, practice level socioeconomic deprivation (≤ median, > median), practice type (single handed or group), patient type (prevalent: known to the practice at baseline or incident: new diagnoses after baseline date), number of co-morbidities (one vs. two or more), presence or absence of IHD, prescribed or not prescribed a statin and cholesterol controlled or uncontrolled at baseline.

